# Study protocol: multimodal physiotherapy as an add-on treatment to botulinum neurotoxin type A therapy for patients with cervical dystonia: DysPT-multi—a prospective, multicentre, single-blind, randomized, controlled study

**DOI:** 10.1186/s13063-021-05705-8

**Published:** 2021-10-25

**Keywords:** Cervical dystonia, Spasmodic torticollis, Physical therapy, Physiotherapy, Botulinum neurotoxin, Treatment, Rehabilitation

## Abstract

**Background:**

Botulinum neurotoxin (BoNT) is currently the best therapeutic option in the treatment for cervical dystonia (CD). Additional treatments like physiotherapy (PT) may even improve the results of the BoNT injection with type A (BoNT-A), but there are no definite recommendations. In the last few years, some studies showed tendencies for PT as an adjuvant therapy to benefit. However, high-quality studies are required.

**Methods:**

This study is a multicentre, randomized, single-blind, controlled trial to demonstrate the effectiveness of a multimodal PT program compared to a nonspecific cupping therapy, additionally to the BoNT-A therapy. Two hundred participants will be assigned into the multimodal PT plus BoNT intervention arm or the BoNT plus cupping arm using randomization. Primary endpoint is the total Score of Toronto Western Spasmodic Rating Scale (TWSTRS). Secondary endpoints are the mobility of the cervical spine (range of motion, ROM), the TWSTRS subscales, and the quality of life (measured by questionnaires: CDQ-24 and SF-36). Patients will be single-blind assessed every 3 months according to their BoNT injection treatment over a period of 9 months.

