### Sample size {14}

In the pilot trial [19], total TWSTRS reduced on average by 8.7 points after the PT plus BoNT intervention. Standard deviations for BoNT and PT plus BoNT intervention were 7.4 and 5.4 points, respectively. To detect a difference of at least three points between the two groups with a power of 90%, 100 patients per group should be analyzed. Assuming a drop-out rate of 10%, a total of 224 patients (112 per group) should be randomized in the trial.

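### The abstract gives 200 as the number to be randomised, but the sample size section derives 200 as the number to be analysed and 224 as the number to be randomised

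*Protocol article*

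**What the plan says.** Two places in the protocol article give a total sample size.

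- Abstract, Methods: "Two hundred participants will be assigned into the multimodal PT plus BoNT intervention arm or the BoNT plus cupping arm using randomization".
- Sample size {14}: for the stated power, "100 patients per group should be analyzed". Then: "Assuming a drop-out rate of 10%, a total of 224 patients (112 per group) should be randomized in the trial".

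The inputs are also in section {14}: "To detect a difference of at least three points between the two groups", at 90% power, with "Standard deviations for BoNT and PT plus BoNT intervention were 7.4 and 5.4 points, respectively". The section on statistical methods for primary and secondary outcomes {20a} sets the confirmatory significance level at 5% without saying whether the test is one- or two-sided. It plans a linear mixed model with baseline TWSTRS total score as a covariate. The section on non-adherence and missing data {20c} makes the primary analysis intention-to-treat, with all randomised patients included.

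**The concern.** Both sentences describe the same quantity, patients allocated to an arm by randomisation, and give different totals: 200 and 224. They cannot both be the target. Shortening for an abstract could explain leaving out the drop-out allowance. It does not explain attaching the number to be analysed to the act of randomisation.

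The number to randomise tells the centres when to stop recruiting, and later readers will use it to judge whether the trial reached its planned size. By the article's own dates (recruitment from June 2020, completion expected in 2022, publication in October 2021), recruitment was still open when both figures appeared. If the abstract's figure were followed, the drop-out reserve built into the sample size section would disappear.

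**Working it through.** **Inputs, all from Sample size {14} unless noted**

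- Difference to detect: 3 points on the TWSTRS total score.
- Standard deviations: 7.4 (BoNT) and 5.4 (PT plus BoNT).
- Power: 90%. Drop-out: 10%. Equal groups.
- Significance level: 5% (section {20a}). Two-sided is assumed here, because a one-sided 5% test needs only 80 per group and so does not match the article's 100.

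**Step 1: reproduce the number to be analysed**

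Normal approximation, per group:

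n = (1.960 + 1.2816)² × (7.4² + 5.4²) / 3² = 10.507 × 83.92 / 9 = 97.98, so 98.

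The unequal-variance (Welch) t-test, evaluated with the noncentral t distribution, needs 100 per group, with power 90.3%. The article's figure of 100 is reproduced.

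**Step 2: reproduce the number to be randomised**

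100 / (1 − 0.10) = 111.1, rounded up to 112 per group; 2 × 112 = 224. This is also reproduced. Section {14} is internally correct, so the abstract is the figure out of line.

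**Step 3: what 200 randomised would mean on the same calculation**

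Patients left after 10% drop-out: 200 × 0.90 = 180, or 90 per group.

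Normal approximation: standard error = √(83.92/90) = 0.966; 3/0.966 = 3.107; 3.107 − 1.960 = 1.147; power = Φ(1.147) = 87.4%.

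| Randomised | Left per group after 10% drop-out | Power, normal approximation | Power, Welch t |
|---|---|---|---|
| 224 | about 100 | 90.6% | 90.3% |
| 200 | 90 | 87.4% | 87.0% |

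On the Welch figures the type II error goes from 9.7% to 13.0%.

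**Step 4: sensitivity to the planned baseline adjustment**

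The figures above are for an unadjusted two-group comparison, whereas section {20a} plans a baseline-adjusted model. The article gives no correlation r between baseline and outcome, and does not say whether 7.4 and 5.4 describe scores or changes, so the following is a range under assumption. If they are standard deviations of post-treatment scores, adjustment multiplies the variance by (1 − r²). If they are standard deviations of change, with equal variance before and after, it multiplies the variance by (1 + r)/2. Power at 90 per group:

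| Reading of the standard deviations | Assumed r | Power |
|---|---|---|
| Post-treatment scores | 0.2 | 88.3% |
| Post-treatment scores | 0.31 | 90.1% |
| Post-treatment scores | 0.5 | 94.6% |
| Change | 0.5 | 94.6% |
| Change | 0.8 | 90.2% |
| Change | 0.9 | 88.7% |

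So 90 per group could still reach 90% under the planned model, but that depends on a correlation the article does not state.

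**The case against.** The strongest reply is that the operative text is section {14}, which is clear and correct, and that the abstract has merely quoted the analysed number. The sections on recruitment, sequence generation and trial status give no target of 200, so nothing shows that the trial would stop there. This stands as a limit on severity. It does not remove the contradiction, since the abstract's sentence is about allocation and no other text corrects it.

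A second reply is that the intention-to-treat analysis includes all randomised patients, so nobody is lost. The sample size section itself treats drop-outs as not analysed, and that is how it gets from 200 to 224. The 87% figure follows that logic, but it does assume that drop-outs contribute no primary outcome data.

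A third reply is that baseline adjustment may restore the power. It may, as the range above shows. The stated calculation claims no such gain, so 90% at 200 randomised cannot be taken from the article as it stands.

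In the other direction, a reader might infer that the trial is underpowered, that its 90% power is lost, or that 200 randomised could keep 90% only with drop-out of about 1% or less. The article does not support these as general statements. The shortfall is about 3 percentage points. It arises only if recruitment actually stops at 200, and it belongs to the unadjusted calculation, as does the 1% limit.

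**Conclusion.** The inconsistency is real: the abstract reports the number to be analysed as the number to be randomised. The sample size calculation itself contains no error. The practical size is modest, a fall from 90% to about 87% power. That figure rests on recruitment ending at 200, 10% drop-out without primary outcome data, equal allocation, a two-sided 5% test, and no credit for baseline adjustment. The design, the analysis model and the derivation in section {14} are unaffected. It is an abstract-to-body inconsistency of moderate to low severity, worth correcting because it concerns the recruitment target of a confirmatory trial.

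**What to change.** Change the sentence in the abstract to say that 224 participants (112 per group) will be randomised so that 200 (100 per group) can be analysed. This costs one sentence and adds no patients beyond those already planned in section {14}.

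If 200 is in fact the randomisation target, leave the abstract and change section {14} instead: state 200 randomised and about 180 analysed at 10% drop-out, and give the power as about 87% on the unadjusted calculation. If credit for baseline adjustment is to be claimed, state the assumed correlation and its source.

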**Discussion:**

The study aims to determine the effectiveness and therefore potential benefit of an additional multimodal physiotherapy for standardized treatment with BoNT-A in patients with CD, towards the BoNT-therapy alone. This largest randomized controlled trial in this field to date is intended to generate missing evidence for therapy guidelines.

**Trial registration:**

The study was registered in the German Clinical Study Register before the start of the patient recruitment (DRKS00020411; date: 21.01.2020).

## Introduction

### Background and rationale {6a}

Cervical dystonia (CD) usually occurs as primary adult-onset dystonia between 30 and 50 years. CD represents the largest part of primary dystonia syndromes with an estimated prevalence between 2.8 and 18.3 per 100,000 [1]. Dystonia is characterized by involuntary patterned contractions, which often lead to abnormal postures or movements [2]. In the case of CD, this affects cervical and neck muscles, which results in an abnormal head or neck position or motion [3]. The majority of all patients also suffer from pain [4] and further from non-motor symptoms like depression or social phobia [5, 6]. Therapeutic options are purely symptomatic and not causal, meaning that only an alleviating of the symptoms is possible. Therapy of choice is a selective peripheral denervation of the affected muscles using botulinum neurotoxin (BoNT). The BoNT “Abobotulinumtoxin A” is injected into the affected muscles in individual doses. This leads to a temporary weakening or paralysis of the corresponding muscles. The injection must therefore be repeated regularly at 3-month intervals. The BoNT therapy is effective, well-tolerated and safe for patient with CD [7, 8]. At present there are no specific recommendations for physiotherapy (PT) in CD [9, 10]. The effects of additional physiotherapy in CD-patients have only rarely been examined to date and the quality of available evidence is ranged from very low to low [11]. De Pauw et al. published a review of six clinical trials and ten case series [12]. However, the different physiotherapy techniques, duration of interventions, and outcome measures made it difficult to compare study data and results of these trials. Four of the studies were evaluated with a moderate or high quality by De Pauw et al. [13–16]. These four trials, on 20 to 40 patients, showed a trend towards a benefit of the physiotherapy program in the Toronto Western Spasmodic Rating Scale (TWSTRS) subscores, the SF-36 score, and the rotation deviation. De Pauw et al. concluded that multimodal physiotherapy concepts with the main focus on active exercises in combination with BoNT type A (BoNT-A) treatment probably have a beneficial effect on pain, severity of the CD, and activities of daily life. However, the authors report that further studies are required before any specific recommendations can be given [11, 12]. Under the assumption that add-on PT results in a better outcome, two RCTs examined a special PT technique (Bleton regime) vs. regular PT [17, 18]. The results showed that there were no significant differences between the different PT interventions, though both groups in each of these two studies showed improvements, especially in TWSTRS and generic quality of life after different add-on PT intervention [17, 18]. A recent pilot study with 18 patients was also able to show clear advantages of additional PT [19]. There were significant improvements in mental health (SF-36), in the rotation and flexion/extension dimension of the cervical spine ROM and in every TWSTRS subscore following PT intervention consisting of two PT sessions per week over a period of 12 weeks [19]. From the data available at present, it can be concluded that multimodal add-on PT, which focuses on active exercises, has an advantage in terms of pain, severity of CD, and activities of daily life compared to the sole BoNT therapy. However, in order to give clear recommendations, further, in particular RCTs with a large number of participants are required [9, 10, 18].

### Objectives {7}

The main objective is to determine the effect of the multimodal physiotherapy as an add-on treatment to BoNT-A therapy for patients with cervical dystonia on the disease expression of cervical dystonia. Secondary objectives are effects on the statics and mobility of the cervical spine and on disease-specific and disease-unspecific health perception.

### Trial design {8}

This study is planned as a multicentre, randomized, single-blind, controlled trial.

## Methods: participants, interventions and outcomes

### Study setting {9}

University Hospital, Outpatient clinic of the Department of Neurology / Institute for Physiotherapy, Jena, Germany

University Hospital, Centre for Neurodegeneration/ Dystonia outpatient clinic, Tübingen, Germany

Two more study centers are planned. All parties involved obtain the same study procedures and devices including the according training of the measurement.

### Eligibility criteria {10}

Study population:
Adult patients diagnosed with CDAlready treated with BoNT therapyInclusion criteria:
CD diagnosed, based on Col/Cap-classification [3]Continuously treated with BoNT-A in approximately 3 months’ interval (11 to 13 weeks; aiming to prevent bias by using different BoNT-A-products with different dosing strategies)—independent of a special dilution or concentration of the BoNTAt least 12 months’ treatment without BoNT-A scheme changes over the last 3 injectionsSigned patient informed consentExclusion criteria:
CD with antecollis/-caput onlyCD with dystonic tremor onlyPT intervention within the last 3 months before study onset (previous PT is possible, but not necessary for participation)Contraindications for physiotherapy treatmentContraindications for BoNT-A treatment

### Who will take informed consent? {26a}

The medical study director (principal investigator) of the respective study center will take informed consent.

### Additional consent provisions for collection and use of participant data and biological specimens {26b}

Not applicable.

### Interventions

#### Explanation for the choice of comparators {6b}

From the data available at present, it can be concluded that multimodal add-on PT, which focuses on active exercises, has an advantage in terms of pain, severity of CD and activities of daily life compared to the sole BoNT therapy. Participants will be assigned into the multimodal PT plus BoNT intervention arm or the BoNT plus cupping arm using randomization. Cupping therapy was chosen as comparator (control group) to compare with a technique, which includes the presence of a therapist using a passive application on not directly by cervical dystonia affected muscles. In addition, cupping therapy reduces chronic neck pain, which is common in CD patients [20]. However, there is no evidence that cupping therapy affects cervical spine mobility, disease severity, or quality of life in ZD patients. Owing to the nature of the PT intervention, therapists and participants cannot be blinded to treatment allocation. However, the rater assessing the TWSTRS will be blinded for the treatment group of the patient.

#### Intervention description {11a}

Study duration for every participant amounts 9 months which is divided into three periods of 3 months each. In the first period, both groups will obtain their usual BoNT treatment. In the second phase, the respective intervention starts. In this time, the intervention arm conducts the add-on multimodal PT program that includes 24 PT sessions while the control arm receives 24 sessions of an add-on unspecific cupping treatment. The third period contains 3 months BoNT treatment for both arms as follow-up period. The participants will be assessed every 3 months according to their BoNT injection intervals. That means there are four assessment time points: at the beginning of period one, at the start of the intervention period, at the end of the intervention period respectively the start of the third period, and at the end of the third period.

Patients can choose their own physiotherapists. Moreover, every physiotherapist receives a therapy recommendation (Table 1). They are not obliged to use every mentioned technique, but they should assign their therapy to different proposals with regard to the evaluation.

**Table 1 Tab1:** Therapy recommendation of physiotherapy (intervention group)

Muscular	Neuromuscular	Peripheral approaches
□ Mobilization of the cervical spine (passive-active)	□ Multidimensional movement therapy: o with visual control o without visual control	□ Posture training
□ Isometric technique (of antagonists)		□ Perception training
□ Muscle relaxation (stretching etc., gentle)	□ PNF: diagonals of shoulder blades, upper extremity, head, etc.	□ Relaxation techniques
□ Treatment of trigger points (gentle)		□ Whole-body tension/ stem management
	□ Balance training	
	□ Coordination training	

##### Group A: Intervention: physiotherapy—24 therapy units, two times weekly for a duration of 30 minGroup B: Control: cupping therapy (dry, CT)

Target of the CT is hyperemia and metabolic activation for self-regulation of the connective tissue. Moreover, pain relief and relaxation are further goals of the CT. The maximum duration is about 15 min or in case of clear formation of a hematoma or by dropping of the glasses. The therapy shall be applied to the patients’ shoulder girdle, in particular the rotator cuff (*Musculus infraspinatus and supraspinatus*), the rhomboids (*Musculus rhomboideus major et minor*) and the chest muscles (*Musculus pectoralis major*).

#### Criteria for discontinuing or modifying allocated interventions {11b}

The DysPT-Multi study is an interventional study but not a clinical drug trial in humans. There are few risks associated with study therapy, but patients receive BoNT-A (not an investigational drug, but an interventional medicinal product) as standard. This concomitant medication carries known risks. As the study is conducted in accordance with the Declaration of Helsinki and following the ICH-GCP guideline, the establishment of a safety management with regard to the study therapy and the BoNT-A administration has been implemented. For this purpose, adverse events observed in the course of the clinical study will be recorded and evaluated by the study centers and regularly re-evaluated by the study director with regard to the causal relationship to the study therapy or the BoNT-A administration. In the context of individualized physiotherapeutic treatment, a high level of patient safety can be assumed. Adverse events are more likely to occur for standard therapy with BoNT-A.

#### Strategies to improve adherence to interventions {11c}

Physical therapy practices will be provided with contact information for study centers for consultation and follow-up.

#### Relevant concomitant care permitted or prohibited during the trial {11d}

Concomitant therapy or medication will be queried and noted. With regard to the intention-to-treat-analysis, the change of medication during the study duration will be noted as test plan deviation/ query. Nevertheless, the patient will stick to its study group until the study ends.

#### Provisions for post-trial care {30}

Not applicable.

### Outcomes {12}

Primary endpoint:
Total score of the Toronto Western Spasmodic Rating Scale (TWSTRS)

Secondary endpoints:
TWSTRS severity, disability, and pain scoreMobility of the cervical spine using an inertial measurement unit (ROM)SF-36 to evaluate the generic healthCDQ-24 to evaluate disease-specific quality of life [16]Subgroup analysis on age, severity, disease duration, BoNT-A treatment duration

### Participant timeline {13}

Participant timeline is shown in Table 2 and Fig. 1

**Table 2 Tab2:**
[figure not shown]
Schedule of enrolment, interventions, and assessments (SPIRIT figure)

**Fig. 1 Fig1:**
[figure not shown]
study timeline

.

### Sample size {14}

In the pilot trial [19], total TWSTRS reduced on average by 8.7 points after the PT plus BoNT intervention. Standard deviations for BoNT and PT plus BoNT intervention were 7.4 and 5.4 points, respectively. To detect a difference of at least three points between the two groups with a power of 90%, 100 patients per group should be analyzed. Assuming a drop-out rate of 10%, a total of 224 patients (112 per group) should be randomized in the trial.

### Recruitment {15}

The medical principal investigator of each study center recruits the patients in the outpatient clinic of the department of neurology.

### Assignment of interventions: allocation

#### Sequence generation {16a}

Computer-generated random number, generated by the software “Random Tool”

An Internet-based randomization tool provided by the Centre for Clinical Studies, University Hospital Jena, will perform the randomization. This will occur after the patient has signed the patient consent form, has met all inclusion and no exclusion criteria, and therefore has been included in the study.

#### Concealment mechanism {16b}

The group allocation is assigned by the medical study director of the respective study center. The patient obtains the respective treatment information to hand it over to their therapist.

#### Implementation {16c}

By the medical study director of the respective study center.

### Assignment of interventions: blinding

#### Who will be blinded {17a}

Outcome assessors (for every patient is measured in the same way and there are no special assessments concerning the intervention group)

#### Procedure for unblinding if needed {17b}

Not applicable.

### Data collection and management

#### Plans for assessment and collection of outcomes {18a}

The assessors are especially trained before start of the recruitment and/ or were already experienced in the different measuring methods.

The primary endpoint of the study is the total score of the Toronto Western Spasmodic Torticollis Rating Scale (TWSTRS). The TWSTRS disease-specific scoring system was developed to describe the severity of CD [21]. This measurement tool is widely used and is explicitly recommended for comparing studies or performing meta-analyses [2, 12]. Validity and reliability of the score could be confirmed [21]. In this study, the TWSTRS is collected in a blinded manner by examination. The total score range is 0–85, with a high score representing greater expression or impairment [22].

Secondary endpoints are the TWSTRS subscales (severity, limitation of daily life, and pain), the range of motion (ROM) of the cervical spine assessed by three-dimensional motion analysis using inertial sensors (Company: Velamed), the SF-36 questionnaire [23] to assess generic health perception, and the CDQ-24 questionnaire [24] to assess disease-specific quality of life. Furthermore, a subgroup analysis by age, severity, duration of disease, and duration of BoNT treatment is planned.

The effect of an add-on multimodal PT will be investigated with regard to the individual subscales of the TWSRTS in order to present more specific effects, if necessary.

The clinical correlate of cervical dystonia is the cervical spine misalignment or malposition, including the adjacent muscles and joints. Thus, the statics and mobility of the cervical spine represent an important parameter for assessing the effect of the intervention. In order to be able to obtain data that are as objective as possible, the three-dimensional instrument-based measurement system (company: Velamed) determines the extent of cervical motion for this endpoint. This system is based on ultrasound measurement signals and can accurately determine movements in all three planes of motion. The validity and the reproducibility have been successfully tested [25]. Another measurement instrument with a similar technical basis and accurate motion analysis could already be evaluated in patients with CD and was recommended for diagnosis as well as for progress documentation [26]. Furthermore, a measurement system (company: Zebris) that works similarly to the three-dimensional motion measurement was successfully used for motion analysis in the pilot study [19]. However, the measurement with inertial sensors is more precise.

The SF-36 provides the study with a cross-disease score system to assess quality of life. Validity and reproducibility have been tested [23].

To assess disease-specific health perception, the CDQ-24 questionnaire is used. This questionnaire was developed to assess the quality of life of patients with CD and/or blepharospasm. The original questionnaire is available in German. Validity and reliability are available [24].

